## Abstract

**Background::**

Lung cancer screening in high-risk population increases the proportion of patients diagnosed at a resectable stage.

**Aims::**

To optimize the selection criteria and quality indicators for lung cancer screening by low-dose CT (LDCT) in the Czech population of high-risk individuals. To compare the influence of screening on the stage of lung cancer at the time of the diagnosis with the stage distribution in an unscreened population. To estimate the impact on life-years lost according to the stage-specific cancer survival and stage distribution in the screened population. To calculate the cost-effectiveness of the screening program.

**Methods::**

Based on the evidence from large national trials - the National Lung Screening Trial in the USA (NLST), the NELSON study, the recent recommendations of the Fleischner society, the American College of Radiology, and I-ELCAP action group, we developed a protocol for a single-arm prospective study in the Czech Republic for the screening of high-risk asymptomatic individuals. The study commenced in August 2020.

**Results::**

The inclusion criteria are: age 55 to 74 years; smoking: ≥30 pack-years; smoker or ex-smoker <15 years; performance status (0–1). The screening timepoints are at baseline and 1 year. The LDCT acquisition has a target CTDIvol ≤0.5mGy and effective dose ≤0.2mSv for a standard-size patient. The interpretation of findings is primarily based on nodule volumetry, volume doubling time (and related risk of malignancy). The management includes follow-up LDCT, contrast enhanced CT, PET/CT, tissue sampling. The primary outcome is the number of cancers detected at a resectable stage, secondary outcomes include the average cost per diagnosis of lung cancer, the number, cost, complications of secondary examinations, and the number of potentially important secondary findings.

**Conclusions::**

A study protocol for early detection of lung cancer in Czech high-risk asymptomatic individuals (ELEGANCE) study using LDCT has been described.

## Introduction

1

The annual incidence rate of lung cancer in the Czech Republic is high, 86 and 43 cases per 100,000 men and women a year, respectively.^[1]^ With more than half of the cases diagnosed in stage IV, the relative 5-year survival is only 10% making it the most common cause of death among oncological diagnoses. Cigarette smoking is a well-documented cause of lung cancer and about 90% of lung cancers are directly caused by smoking. The relationship between the number of cigarettes smoked per day, the depth of inhalation, the age of the smoker, and the development of lung cancer have been documented.^[2]^

Vast resources have been dedicated to shifting the diagnosis of bronchogenic cancer to its early stages. Poor survival can be largely attributed to delayed diagnosis. Only small resectable stage I tumors offer favorable prognosis with 5-year survival rates of 70% to 90%.^[3]^

In the United States, where lung cancer screening is an established and recognized tool, smoking prevalence is only 15 percent. In the Czech Republic where every fourth adult and about 12% of primary school pupils are active smokers, there is no screening for lung cancer yet. Because of the unsatisfactory results of anti-smoking intervention programs and the fact that even more lung tumors are becoming diagnosed in former (non-active) smokers, secondary prevention by early detection of lung cancer by screening in a selected population is proposed.

Based on previous studies, including the National Lung Screening Trial in the USA (NLST),^[4]^ the NELSON study,^[5]^ and on the recent recommendations of the Fleischner society,^[6]^ the American College of Radiology^[7]^ and I-ELCAP action group,^[8]^ we developed a protocol for an optimization study in the Czech Republic for the screening of high-risk asymptomatic individuals by low-dose CT (LDCT).

## Study protocol

2

The study was approved by the Ethics Committee of the General University Hospital in Prague (12/19 Grant AZV VES 2020 VFN). The study adheres to the principles of the Declaration of Helsinki. Written, informed consent to participate will be obtained from all participants. Patients may discontinue at any time. The participants are being recruited by family physicians, pneumologists, and self-referred by an advertising campaign. The study is designed as a single-arm prospective study conducted in an academic hospital. The study is registered under ClinicalTrials.gov ID: NCT04627350. Protocol modifications will be announced to the trial registry and the Ethics Committee.

### Study aims

2.1

The aims of this project are:

1.to optimize selection criteria and quality indicators for the target population for lung cancer screening in the Czech population2.to compare the influence of screening on the stage of lung cancer at the time of the diagnosis with the stage distribution in an unscreened population3.to estimate the impact on life-years lost according to the stage-specific cancer survival and stage distribution in the screened population4.to calculate the cost-effectiveness of the screening program5.to assess the potential for opportunistic screening of non-communicable diseases.

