#### Secondary objectives

2.2.2

1.The average cost per diagnosis of lung cancer at a resectable stage2.Number, cost, complications of secondary examinations – follow-up LDCT, PET/CT, bronchoscopy, tissue sampling3.Number of potentially important secondary findings (e.g., pulmonary fibrosis, aortic aneurysm, compression fracture and signs of osteoporosis,^[9,10]^ myocardial scar) previously unknown.

The study is designed as 2 screening rounds at a baseline and at 1 year, the estimated study duration is 4 years with 2 years of enrolment to baseline screening, 1 year for second round screening, and 1 year for follow-up of the second round. The study commenced in August 2020. Study data are entered to a secured enterprise database, which can be accessed by all investigators. The first author is responsible for data monitoring, integrity, and auditing on a monthly basis. Nominal data will be presented as numbers and percentages and will be analyzed using the Fisher test. Ordinal and continuous data will be reported as mean ± standard deviation or 95% confidence intervals. The study results will be published in a peer-reviewed journal. Authorship will be based on the ICMJE guidelines.

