### Sample size

2.3

In comparison with the Nelson study, where 2.1% scans were positive and 0.9% were cancers detected in the first round, we define a study population at greater risk and expect that the number of detected cancers would be greater. In the Nelson study 58.6% of cancers were detected at stage I compared to 13.5% in the control group. According to the Czech cancer registry, only 10.5% of lung cancers are detected in stage I.^[1]^ To compare these outcomes, the study would require 15 patients with detected cancer, about 1500 screened patients to achieve a power of 80% at a 0.05 significance level. For an expected adherence of 90% and the optimization of input values, we estimate the sample size at 2500 participants. This study is designed as observational, therefore it has no control arm and it has no ambition to assess the effect of lung screening on mortality such as in the NELSON trial with a sample size calculated between 17,300 and 27,900 participants.^[11]^

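### The life-years estimate in aim 3 rests on a proportion-based stage shift, so it counts overdiagnosed stage I cancers, and lead time where survival runs from diagnosis, as benefit

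*Protocol article*

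**What the plan says.** Section 2.1 (Study aims) of the Protocol article lists as its third aim "to estimate the impact on life-years lost according to the stage-specific cancer survival and stage distribution in the screened population"; the abstract repeats it. Both inputs to the calculation are therefore named. The source of the stage-specific survival is not.

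The fourth aim is "to calculate the cost-effectiveness of the screening program". Its effect measure is not stated. The cost outcome that section 2.2.2 does define is "The average cost per diagnosis of lung cancer at a resectable stage".

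Section 2.3 (Sample size) describes the study as observational and continues: "therefore it has no control arm and it has no ambition to assess the effect of lung screening on mortality such as in the NELSON" (the sentence goes on to cite the number of participants which that study needed). It supplies the stage figures used below: "In the Nelson study 58.6% of cancers were detected at stage I compared to 13.5% in the control group", and, from the Czech registry, "only 10.5% of lung cancers are detected in stage I".

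Section 2.2.2 sets two rounds one year apart and an estimated duration of four years, the last being follow-up of the second round.

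**The concern.** Life-years lost depend on when people die. Stage mix and survival after diagnosis are stand-ins for that, and screening changes both even where it postpones no death.

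- **Overdiagnosis.** A cancer that would never have surfaced adds to the stage I count and to the denominator. The stage I proportion rises although no advanced cancer has been prevented.
- **Lead time.** Survival measured from diagnosis lengthens when diagnosis moves earlier, even if the date of death stays the same.

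The choice of survival source does not remove the problem. Survival of clinically diagnosed cases, applied to the screened mix, assumes that the whole stage shift is real. Survival of screen-detected cases contains the lead time directly. With no control arm, and with follow-up too short to observe 5-year survival, the study's own data cannot separate artefact from benefit.

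The Introduction notes that the Czech Republic has no lung cancer screening yet and proposes it. A life-years figure from this study could inform that decision, and an unadjusted one errs in a predictable direction.

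**Working it through.** **Plan's own figures.** The article states no life-years result, so there is none to reproduce. The nearest stated figure, 15 cancers, does reproduce: comparing 58.6% with 10.5%, two-sided 0.05, 80% power, equal groups, no continuity correction, gives 15 per group. The present point does not depend on it.

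**Inputs from the article.** Overall 5-year relative survival 10% and stage I survival 70% to 90% (Introduction); stage I share 10.5% unscreened and 58.6% in the screened NELSON arm (section 2.3).

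**Inputs assumed, because the documents give none.** Overdiagnosis 10%, 20%, 30% of detected cancers; lead time 1, 2, 3 years.

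**Step 1. What the stage-mix method credits in total.** Let s1 be stage I survival. Implied stage II–IV survival is (0.10 − 0.105 × s1) / 0.895. Projected survival at the screened mix is 0.586 × s1 + 0.414 × that value.

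| s1 | Implied II–IV | Projected 5-year survival | Credited gain |
|---|---|---|---|
| 0.70 | 0.030 | 0.422 | 32 points |
| 0.80 | 0.018 | 0.476 | 38 points |
| 0.90 | 0.006 | 0.530 | 43 points |

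This is the whole credited gain, real and artefactual together.

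**Step 2. Overdiagnosis alone.** Let a share *o* of detected cancers be overdiagnosed, all stage I, and let the rest keep the registry mix. The stage I share is *o* + (1 − *o*) × 0.105:

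- *o* = 0.10: 0.10 + 0.0945 = 0.1945
- *o* = 0.20: 0.20 + 0.0840 = 0.284
- *o* = 0.30: 0.30 + 0.0735 = 0.3735

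With the Step 1 survival figures, *o* = 0.10 gives projected survival of 0.1945 × 0.70 + 0.8055 × 0.030 = 0.16, up to 0.1945 × 0.90 + 0.8055 × 0.006 = 0.18. *o* = 0.30 gives 0.28 to 0.34 in the same way. Against 10%, that is 6 to 8 points, or 18 to 24 points, credited with no advanced cancer averted.

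**Step 3. Lead time alone.** Take a constant hazard that gives 10% survival at 5 years: λ = −ln(0.10)/5 = 0.4605 per year. If diagnosis moves L years earlier and death dates do not move, apparent 5-year survival is exp(−λ(5 − L)):

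- L = 1: exp(−1.842) = 0.158
- L = 2: exp(−1.382) = 0.251
- L = 3: exp(−0.921) = 0.398

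In life-years, each case appears to gain L years from diagnosis while the true gain is zero. For 15 cancers that is 15 to 45 life-years.

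**Step 4. Could counts of advanced cancer replace the stage mix?** At the NELSON first-round rate, 2500 × 0.009 × 0.414 = 9.3 stage II–IV cancers would be found at baseline. For a count of 9, the exact Poisson 95% interval is about 4 to 17. The baseline round also brings forward advanced cancers that are already present, which weighs against screening. Such counts are too few, and too distorted, to carry the estimate.

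**The case against.** The strongest reply is that one clause in a list of aims fixes no estimator. The article condenses a fuller protocol, and an adjustment or sensitivity range may stand there or in an analysis plan that is not shown. That is fair as far as it goes: the article's silence does not show that none is planned. But the two inputs are stated, and followed as written they do not identify the quantity claimed.

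Second, whether lead time is credited depends on implementation. If life-years lost are measured from date of death against life expectancy, earlier diagnosis by itself changes little. This stands, and it is why the lead-time part is conditional on survival being counted from diagnosis. The overdiagnosis part needs no such condition.

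Third, Step 1 combines relative survival for all cases with a range for small resectable stage I tumours from a different source. The implied stage II–IV survival is partly a product of that mixing. This also stands: the 32 to 43 points show how the method works and are not an estimate of bias.

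Finally, a reader might infer that aim 3 contradicts section 2.3, particularly if the sentence is cut at "it has no ambition to assess the effect of lung screening on mortality". The full sentence disclaims a mortality assessment of the NELSON kind, with the sample size that needs. A study can decline to measure mortality and still project it. The two sit in tension, because life-years lost is a mortality quantity with no control arm behind it, but they do not contradict each other.

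**Conclusion.** The concern holds as a bias in one direction in a stated aim. Unadjusted, the stage-mix calculation favours screening by an amount that the study cannot measure. Under the assumed values, overdiagnosis alone lifts the stage I share from 10.5% to 19–37%, and lead time alone lifts apparent 5-year survival from 10% to 16–40%. Both ranges rest on assumptions: all overdiagnosed cases in stage I, no true shift, constant hazard, unchanged death dates.

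Two wider readings are not supported. A reader might infer that the cost-effectiveness result inherits the bias, but nothing in the article ties aim 4 to these life-years, and the defined cost outcome is per resectable-stage diagnosis. A reader might also infer that the main comparison falls. Life-years lost is neither the primary nor a listed secondary objective, so the primary objective and sample size are unaffected by this point.

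**What to change.** - Describe aim 3 as a model-based projection and name the source of the stage-specific survival.
- Label the unadjusted stage-mix result an upper bound with respect to lead time and overdiagnosis.
- Report life-years over a prespecified range, for example lead time of 1 to 3 years and overdiagnosis of 0 to 30% of detected cancers.
- Give absolute stage II–IV counts per 1,000 participants only as a descriptive supplement, for the reasons in Step 4.
- Carry the range into the cost-effectiveness result only if that result uses these life-years.

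The cost is a few model runs and some wording, with no additional participants. The price in results is a smaller and wider estimate of benefit.

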### Study objectives

2.2

#### Primary objective

2.2.1

1)The number of cancers detected at a resectable stage (stage I) vs non-resectable stage (II-IV).

#### Secondary objectives

2.2.2

1.The average cost per diagnosis of lung cancer at a resectable stage2.Number, cost, complications of secondary examinations – follow-up LDCT, PET/CT, bronchoscopy, tissue sampling3.Number of potentially important secondary findings (e.g., pulmonary fibrosis, aortic aneurysm, compression fracture and signs of osteoporosis,^[9,10]^ myocardial scar) previously unknown.

The study is designed as 2 screening rounds at a baseline and at 1 year, the estimated study duration is 4 years with 2 years of enrolment to baseline screening, 1 year for second round screening, and 1 year for follow-up of the second round. The study commenced in August 2020. Study data are entered to a secured enterprise database, which can be accessed by all investigators. The first author is responsible for data monitoring, integrity, and auditing on a monthly basis. Nominal data will be presented as numbers and percentages and will be analyzed using the Fisher test. Ordinal and continuous data will be reported as mean ± standard deviation or 95% confidence intervals. The study results will be published in a peer-reviewed journal. Authorship will be based on the ICMJE guidelines.

### Sample size

2.3

In comparison with the Nelson study, where 2.1% scans were positive and 0.9% were cancers detected in the first round, we define a study population at greater risk and expect that the number of detected cancers would be greater. In the Nelson study 58.6% of cancers were detected at stage I compared to 13.5% in the control group. According to the Czech cancer registry, only 10.5% of lung cancers are detected in stage I.^[1]^ To compare these outcomes, the study would require 15 patients with detected cancer, about 1500 screened patients to achieve a power of 80% at a 0.05 significance level. For an expected adherence of 90% and the optimization of input values, we estimate the sample size at 2500 participants. This study is designed as observational, therefore it has no control arm and it has no ambition to assess the effect of lung screening on mortality such as in the NELSON trial with a sample size calculated between 17,300 and 27,900 participants.^[11]^

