### Inclusion and exclusion criteria

2.4

The pretest risk of lung cancer is dependent especially on the smoking duration, age, sex, family history of lung cancer.^[12,13]^ The inclusion criteria should define a population of participants with the highest risk of lung cancer who are capable of undergoing curative treatment if cancer is found. The recommended threshold by the UK Lung Cancer Screening Trial was based on the prediction result of at least 5% risk of developing lung cancer in the following 5 years.^[12]^

The highest incidence of lung cancer in the Czech Republic is between 60 to 79 years (Fig. 1).^[1]^ The lung screening trials with the highest sample sizes included patients aged approximately between 55 and 75 years of age.^[14]^ The CHEST Guideline and Expert Panel Report recommend the optimal screening 55 to 77 years.^[15]^ The U.S. Preventive Services Task Force recommends annual screening up to 80 years of age, while the Centers for Medicare & Medicaid Services (CMS) end coverage at the age of 77, corresponding to the oldest age at the time of the final annual screen in the NLST. The optimal age span for screening was set to 55 to 74 years to precede the diagnosis of advanced lung cancer and to take into account a shorter life expectancy in the Czech Republic. The male gender carries a higher risk of lung cancer by a factor of 1.5 to 2.^[16]^ This fact is related to a smaller proportion of women, who are heavy smokers and can therefore be equalized by the pack-years inclusion criterion.

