A positive screening test is defined as a high risk finding or intermediate risk finding where verification (PET/CT, tissue sampling, contrast-enhanced CT) was requested. An indeterminate test is defined as low and intermediate risk finding, further managed by LDCT. A negative test (benign appearance or behavior) does not mean that an individual does not have lung cancer.

Secondary findings will be reported as incidental findings and categorized according to their expected clinical significance as shown in Table 4.

**Table 4 T4:** Classification of secondary findings.

SECONDARY FINDINGS	
	Description
1	Normal exam with regard to patient's age, benign variants, clinically unimportant findings
	- e.g., lobus v. azygos, degenerative spine disease, vertebral hemangioma
2	Potentially important findings
	- e.g., pleural effusion, pericardial effusion (>10mm), pulmonary fibrosis, mediastinal lymphadenopathy, pneumonia, emphysema, vertebral compression, aortic aneurysm

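### The only Czech reference for the stage comparison is an unrestricted registry share of 10.5% stage I, so part of the stage shift may reflect eligibility and counting rather than screening

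*Protocol article*

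**What the plan says.** The second aim (Study aims) is to compare stage at diagnosis under screening "with the stage distribution in an unscreened population". The primary objective is "The number of cancers detected at a resectable stage (stage I) vs non-resectable stage (II-IV").

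The Sample size section gives two unscreened figures. One comes from a trial: "In the Nelson study 58.6% of cancers were detected at stage I compared to 13.5% in the control group". The other is Czech: "According to the Czech cancer registry, only 10.5% of lung cancers are detected in stage I". The next sentence sizes the comparison of these figures: "the study would require 15 patients with detected cancer, about 1500 screened patients". The power claimed for it is 80%, with a significance level of 0.05. The section adds that the study is observational and has no control arm.

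Eligibility (Inclusion criteria, Exclusion criteria) is age 55 to 74, at least 30 pack-years, a current smoker or one who stopped less than 15 years ago, and performance status 0–1. Malignancy within 10 years and clinical signs suspicious of lung cancer are excluded. Recruitment includes self-referral through advertising (Study protocol). On age, the article notes: "The highest incidence of lung cancer in the Czech Republic is between 60 to 79 years". On test results it says: "A negative test (benign appearance or behavior) does not mean that an individual does not have lung cancer". No rule is stated for counting a cancer that surfaces after a negative test.

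**The concern.** Without a control arm, the external reference carries the whole stage comparison. The two sides differ in ways unrelated to screening.

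- **Symptoms and fitness.** People who already have suspicious symptoms at entry, or who cannot climb one floor, are kept out of the study. No such restriction is stated for the registry share. Both exclusions can be expected to remove some advanced disease from the study side only.
- **Age, smoking and self-referral.** Eligibility stops at 74, while the article puts peak incidence at 60 to 79. Heavy smoking and self-referral also separate the groups. The article gives no stage distribution by these factors, so they make the groups differ without fixing a direction.
- **Counting.** A registry share covers cases however they came to light. The primary objective counts cancers detected, and does not clearly take in cancers that appear clinically between or after rounds.

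At stake is the size of the stage shift. Aim 3 estimates life-years lost from the stage distribution in the screened population, so an inflated stage I share would carry into it. It could also carry into the cost-effectiveness calculation of aim 4.

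**Working it through.** **Inputs.** From the Sample size section: stage I share under screening p1 = 0.586; registry share p0 = 0.105; trial control share 0.135; power 80%; significance level 0.05; 15 cancers. Sidedness is not stated, and two-sided is assumed below.

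**Step 1: reproduce the 15.** For two equal groups with pooled variance under the null hypothesis and no continuity correction:

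n per group = [1.960·√(2·pm·(1−pm)) + 0.842·√(p1(1−p1) + p0(1−p0))]² / (p1−p0)², where pm = (p1+p0)/2.

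- Against 0.105: pm = 0.3455; n = (1.318 + 0.488)² / 0.481² = 14.1, so **15**. Power at 15 per group is 82.6%.
- Against 0.135: pm = 0.3605; n = (1.331 + 0.505)² / 0.451² = 16.6, so **17**. Power at 15 per group is 75.6%.

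The stated 15 follows from 10.5% and not, by this formula, from 13.5%. The registry share is therefore the likely planning comparator.

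**Step 2: change the reference.** Only the first two rows use figures from the article. The others are assumed shares.

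| Unscreened stage I share | Difference from 58.6% | Cancers per group |
|---|---|---|
| 10.5% (registry) | 48.1 points | 15 |
| 13.5% (trial controls) | 45.1 points | 17 |
| 15% (assumed) | 43.6 points | 18 |
| 20% (assumed) | 38.6 points | 24 |
| 25% (assumed) | 33.6 points | 33 |

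**Step 3: change the count.** Suppose a share f of participants' cancers is found outside screening and has the registry's stage distribution (both assumed). The stage I share of all cancers is then (1−f)·0.586 + f·0.105.

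- f = 0.1: 0.527 + 0.011 = 0.538; 18 per group against 10.5%
- f = 0.2: 0.469 + 0.021 = 0.490; 21 per group
- f = 0.3: 0.410 + 0.032 = 0.442; 27 per group

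**Step 4: false positives if screening had no effect.** The true share in participants is set to the value shown, and the reference is 10.5%. The 38 cancers are an illustration: 2,500 × 0.90 = 2,250 participants, times the 0.9% first-round rate (Sample size) plus the 0.8% per round (Screening interval), which gives 38.25. The nominal rate in the upper tail is 2.5%.

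| True share | Fisher, 15 per group | Fisher, 38 per group | One-sample exact, n = 15 (reject at ≥5) | One-sample exact, n = 38 (reject at ≥9) |
|---|---|---|---|---|
| 13.5% | 0.9% | 2.6% | 4.2% | 6.2% |
| 25% (assumed) | 8.0% | 28.7% | 31.4% | 63.5% |

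The answer depends heavily on the test, on the size of the reference group and on the assumed share. At the article's own alternative of 13.5%, the inflation is small or absent.

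**The case against.** The case on the other side is substantial.

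- **The analysis comparator is inferred.** The 10.5% appears only as a planning input, and neither aim 2 nor the primary objective names a figure. This stands as a limit. But no other Czech reference is named, there is no control arm, and the sample-size text ties the figure to the comparison.
- **Detail left to fuller documents.** An article may leave calendar years, TNM edition and standardisation to the full protocol or analysis plan. That is fair for the bare omission. The point here is the reference that the article does state, which carries no restriction.
- **Symptomatic registry cases belong in the comparison.** Unscreened cancers are largely found through symptoms, so their presence in the registry is not in itself a fault. This stands. The narrower problem is that people already symptomatic at entry are removed from one side only.

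Four stronger readings are tempting and are not supported.

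- A reader might take 13.5% against 10.5% as proof of eligibility bias. The figures come from different sources, and nothing attributes the 3-point gap to eligibility.
- A reader might infer that interval cancers are excluded. No passage excludes them, and a year of follow-up after round 2 is planned. The article simply does not say how they count.
- Table 1 gives a risk below 1% for the benign category, estimated at 90% of participants. This might be read as up to 20 missed cancers (90% of 2,250 = 2,025; 1% of that is about 20). It is an upper bound on risk, in people who return at the one-year round and may be screen-detected there.
- False-positive rates of 31% or 64% need a 25% share that the document does not support, and a one-sample test. The article names the Fisher test. A very large registry group would move Fisher towards those figures, but its size is not stated.

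**Conclusion.** The concern holds as a bias in the estimated size of the stage shift. As written, the plan sets a selected, asymptomatic, fit group of heavy smokers, counted by cancers detected, against a registry share with no stated restriction. The symptom and fitness exclusions, and a count limited to detected cancers, would be expected to favour screening.

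How large the bias is cannot be computed from the document, because the unscreened stage I share of people meeting these criteria is not given. The only documented alternative, 13.5%, takes 3 points off the planned difference (48.1 to 45.1) and adds two cancers per group (15 to 17). Larger effects rest on assumed shares.

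A reader might infer that the stage shift itself is an artefact. The figures do not support that: even an assumed 25% reference leaves a planned difference of 33.6 points. The article's disclaimer about having no control arm concerns mortality. It does not cover the stage comparison, for which power is claimed. The conclusion assumes that the 10.5% will also serve as the analysis reference.

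**What to change.** 1. Replace the unrestricted 10.5% with C34 cases from the same registry, aged 55–74 at diagnosis, from the same calendar years and under the same TNM edition, standardised to the participants' age and sex. The article already shows C34 incidence by age from the national oncology registry, so an age restriction looks feasible.
2. Report the comparison against 13.5% as a sensitivity analysis.
3. Base the main comparison on all lung cancers diagnosed in participants from baseline to the end of the planned year of follow-up after round 2. Show screen-detected cancers separately.
4. State that selection by symptoms, fitness, smoking and self-referral remains uncorrected, so the contrast is not purely a screening effect. Carry that caution into aim 3 and, where it uses the stage distribution, aim 4.

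The cost is one registry extract, follow-up or linkage to find interval cancers (the article describes no linkage arrangement, so this needs checking), and a wording change. The contrast will probably look smaller than 58.6% against 10.5%.

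### Section 2.3 attaches 80% power to 15 detected cancers, a figure that fits two equal groups of 15; the single-arm comparison described has about 99% power

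*Protocol article*

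**What the plan says.** All statements are in the Protocol article.

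- Section 2.3 (Sample size) gives the assumed stage I share with screening and a trial comparator: "In the Nelson study 58.6% of cancers were detected at stage I compared to 13.5% in the control group". It then gives a national comparator: "According to the Czech cancer registry, only 10.5% of lung cancers are detected in stage I".
- To compare these outcomes, it says that "the study would require 15 patients with detected cancer, about 1500 screened patients to achieve a power of 80% at a 0.05 significance level". No test, sidedness, formula or group structure is given for this calculation.
- The same section describes the study as observational and says "therefore it has no control arm". Section 2 (Study protocol) likewise describes a single-arm prospective study.
- Section 2.2.2, after the secondary objectives, names the analysis method: "Nominal data will be presented as numbers and percentages and will be analyzed using the Fisher test".
- The comparison concerned is aim 2 in section 2.1, which sets stage at diagnosis under screening against an unscreened population. The primary objective in section 2.2.1 splits stage I from stages II-IV.

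**The concern.** The 80% is the only operating characteristic the article gives for its main comparison. The number 15 leads to about 1500 screened people and from there to 2500 participants. If 15 and 80% belong to a comparison of two equal samples, they do not describe one screened group set against a registry figure.

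A reader who relies on the statement would take the study to have a one-in-five chance of missing the assumed effect with 15 cancers. In the design described that chance is close to one in a hundred. The reader would also not learn that a stage I share well below the assumed 58.6% would still be declared different from the registry.

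**Working it through.** **Inputs** (section 2.3): p1 = 0.586 (screened), p0 = 0.105 (Czech registry), alternative comparator 0.135 (control group of the earlier trial), alpha = 0.05, power = 0.80, n = 15. Sidedness is not stated.

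**1. Reproducing the plan's 15.** Two-sided pooled z-test, two equal groups, no continuity correction:

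n per group = [z(0.975)·√(2·p̄·(1−p̄)) + z(0.80)·√(p1(1−p1) + p0(1−p0))]² / (p1−p0)²

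with p̄ = (0.586 + 0.105)/2 = 0.3455.

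- First term: 1.960 × √(2 × 0.3455 × 0.6545) = 1.318
- Second term: 0.8416 × √(0.2426 + 0.0940) = 0.488
- n = (1.318 + 0.488)² / 0.481² = 3.263 / 0.2314 = 14.1, rounded up to **15 per group**

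Two other two-group routes also give 15 per group:

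- the one-sided z-test with continuity correction (14.86, rounded up);
- the one-sided 0.05 Fisher test, where power is 77.2% at 14 and 81.3% at 15.

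Against 13.5%, the two-sided pooled formula gives 17, so the figure fits the registry's 10.5%.

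**2. One-sample formulas.** Against a fixed 10.5%, two-sided normal approximation:

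n = [(1.960·√(0.105 × 0.895) + 0.8416·√(0.586 × 0.414)) / 0.481]² = [(0.601 + 0.415)/0.481]² = 4.5, so 5.

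The normal and arcsine variants tried give 4 to 7, and the exact binomial gives 6 to 9. None gives 15.

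**3. Power of the design described.** X ~ Bin(15, p), tested against p0 = 0.105, with an upper tail of at most 0.025:

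- P(X ≥ 4 | 0.105) = 0.065, too large; P(X ≥ 5 | 0.105) = 0.0155. Reject at 5 or more stage I cancers.
- Power: P(X ≥ 5 | 0.586) = **98.7%**.
- Solving P(X ≥ 5 | p) = 0.80 gives p = 0.408, a true stage I share of **about 41%**.
- Against 13.5% the cut-off is 6 or more, and power is 95.7%.

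Power at small n moves unevenly because the test is discrete: 80.1% at n = 6, 68.3% at n = 7, 80.4% at n = 8 and 88.4% at n = 9.

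Fisher's test of 15 cancers against a large registry sample gives nearly the same power: 98.8% with an assumed 300 registry cases and 98.7% with an assumed 6000.

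**4. Power if two groups of 15 were meant.** Fisher test, full enumeration of both binomials:

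| Per group | Two-sided 0.05, vs 10.5% | One-sided 0.05, vs 10.5% | Two-sided 0.05, vs 13.5% |
|---|---|---|---|
| 15 | 69.7% | 81.3% | 60.2% |
| 17 | 78.9% | 87.9% | 70.7% |
| 18 | 82.8% | 90.5% | 75.4% |
| 20 | 88.1% | 93.4% | 81.1% |

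**5. Cancers expected at the planned size.** 2500 × 0.90 × 0.009 = 20.25 from one round at 90% adherence, and 2500 × 0.009 = 22.5 at full adherence. With 20 cancers against a fixed 10.5%, rejection is at 6 or more and power is 99.8%.

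**The case against.** The article fixes neither the test nor its sidedness for this calculation, so the two-group origin of 15 is inferred. A journal article may also leave the derivation to a full protocol that is not shown. One reading matches the published figures well: a one-sided 0.05 Fisher test reaches 80% at 15 per group, and Fisher is the test named in section 2.2.2. A reader might infer that 80% is wrong for the Fisher test on any reading, or that 15 can come only from an uncorrected chi-square. The documents support neither inference, because sidedness is open and three two-group routes give 15.

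Treating the registry share as fixed is also an assumption, because no registry count is given.

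A further tempting inference is that the study is too small. It does not follow. About 20 cancers are expected from one round alone at 0.9%, two rounds are planned, and even a two-sided Fisher test on 20 against 20 would have 88% power. Nor is the step from 15 cancers to 1500 people part of the error. It implies a 1.0% yield, and section 2.3 expects more cancers than the earlier trial's 0.9%.

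What remains is that every route found to 15 needs a second group of 15. The article rules out a control arm, and against a registry the power is near 99% whether the reference is fixed or a large sample. This is a stated figure that conflicts with the stated design, so it is more than an omitted detail.

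**Conclusion.** The point holds as a mismatch between a power statement and the design it is meant to describe. At 15 cancers the comparison with the registry has about 99% power if the true share is 58.6%, and the 80% level corresponds to a true share of about 41%. For two groups of 15, the two-sided Fisher test falls about 10 points short (69.7%) and needs 18 per group. The one-sided version reaches 81.3%, but only with a group the study does not have.

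This rests on three assumptions: 10.5% is the comparator, it is fixed or comes from a large registry sample, and the exact test allows an upper tail of 0.025. The two-group origin of 15 is an inference, but the 99% figure does not depend on it.

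For the single-arm comparison the error is conservative, and no decision on enrolment turns on it. Severity is minor to moderate.

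**What to change.** In section 2.3:

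- Name the test, its sidedness and the comparator. The comparator is either the registry proportion as a fixed reference (exact one-sample binomial test) or the actual registry counts (Fisher test).
- Replace the 80% with the figure that matches. For the exact binomial test against 10.5%, that is about 99% power at 15 cancers, or a detectable stage I share of about 41% at 80% power.
- Optionally, add the expected exact 95% confidence interval for the stage I share, for example 32% to 84% for 9 of 15 or 36% to 81% for 12 of 20. This would inform readers about precision, but the correction does not depend on it.

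The cost is rewording one paragraph. Enrolment, the screening schedule and data collection do not change.
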